#### Methods in analysis to handle protocol non-adherence and any statistical methods to handle missing data {20c}

To evaluate the influence of non-adherence (treatment adherence < 80% based on pill-count), an on-treatment analysis will be performed in addition to the ITT analyses. Missing outcome variables will not be imputed since mixed models can handle these missing data. In case of missing data in relevant covariates, multiple imputation with predictive mean matching (PMM) will be performed.

#### Plans to give access to the full protocol, participant level-data, and statistical code {31c}

Access to the full study protocol and statistical scripts can be requested after study finalization and publication. Coded participant level data will only be shared in case of consent and compliance with the established consortium agreement.

#### Composition of the data monitoring committee, its role and reporting structure {21a}

A data safety monitoring board or safety committee is not established for this study since this is a low risk study. On site monitoring of all study sites is performed regularly by an independent monitor of the Clinical Research Bureau (CRB) of the Amsterdam UMC, location VUmc as explained in more detail in the section “Frequency and plans for auditing trial conduct (Spirit Guidance {23})”. For more information, visit https://www.amsterdamumc.org/en/research/support/about/clinical-research-monitoring.htm.

#### Adverse event reporting and harms {22}

The following, prespecified AEs, reported spontaneously by the subject or observed by the investigator or research staff will be recorded within the electronic case report forms (eCRF): gastro-intestinal complaints, muscle weakness, arrhythmias, fractures, somnolence, dizziness, tooth discoloration, disturbance of taste, plasma magnesium <0.5 or >1.5 mmol/L or plasma phosphate <0.7 or >1.6 mmol/L. A short questionnaire is administered at 6 and 24 weeks of intervention, evaluating self-reported side effects and convenience, based on two domains of the Treatment Satisfaction Questionnaire for Medication-14 (TSQM-14); see Additional file 2 [52]. AEs will be presented as descriptive data in a table split by allocation arm.

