#### Criteria for discontinuing or modifying allocated interventions {11b}

Criteria for discontinuation or stepwise modification of the intervention in the context of safety evaluation and intolerable side effects, including subsequent follow-up, are summarized in Fig. 1.

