#### Strategies to improve adherence to interventions {11c}

Medication intake, tolerability, and adherence is actively assessed during each study visit. Pill count will be performed at 12 and 24 weeks of intervention. Subjects will be considered compliant based on pill count when they take at least 80% of the study medication. In addition to plasma levels of magnesium and phosphate, also 24-h urinary magnesium and phosphate concentrations at baseline and after 24 weeks of intervention will be supportive in the evaluation of adherence.

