### Assignment of interventions: blinding

#### Who will be blinded {17a}

The randomized, double-blind design ensures that participants as well as the research team and care providers will be blinded for the magnesium citrate intervention. The magnesium citrate and placebo identification list will only be available to concerning research pharmacies. Randomization for the additional SFOH prescription is open-label and therefore known to all involved. Data analyses will be performed before revealing the randomization code.

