#### Plans to promote participant retention and complete follow-up {18b}

To promote participant retention and complete follow-up, contact through phone and email is encouraged and planning of visits are confirmed through email. Also, great effort is made to combine regular laboratory or physician hospital visits with research measurements to facilitate research investment. Participants who discontinue participation after the start of the intervention will be asked to accept the T3 PWV measurement to allow ITT analysis of the primary endpoint. Protocol deviations regarding the intervention will be handled in the analyses differentiating between ITT and on treatment analyses.

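### Tolerability is actively checked at every visit, but listed AEs are recorded only if volunteered or observed. With open-label SFOH and no harm assessment named for leavers, the by-arm side-effect data may be inconsistent.

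*Protocol article*

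**What the plan says.** Four parts of the protocol article bear on how side effects reach the comparison between arms.

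- **Adherence {11c}:** "Medication intake, tolerability, and adherence is actively assessed during each study visit".
- **Harms {22}:** "prespecified AEs, reported spontaneously by the subject or observed by the investigator or research staff will be recorded" in the eCRF. The same section adds the questionnaire: "A short questionnaire is administered at 6 and 24 weeks of intervention, evaluating self-reported side effects and convenience". The planned output is descriptive: "AEs will be presented as descriptive data in a table split by allocation arm".
- **Blinding {17a}:** "Randomization for the additional SFOH prescription is open-label and therefore known to all involved". Magnesium and its placebo are double blind.
- **Retention {18b} and discontinuation {11b}:** people who discontinue participation after starting treatment "will be asked to accept the T3 PWV measurement to allow ITT analysis of the primary endpoint". Separately, for stopping or modifying treatment, the criteria for "safety evaluation and intolerable side effects, including subsequent follow-up, are summarized in Fig. 1". That figure is not reproduced in the text available for this review.

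The limitations paragraph of the Discussion accepts the open-label SFOH on the ground that the primary and secondary outcomes are standardised measurements. It does not mention AEs.

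**The concern.** The adherence section and the harms section describe two different routes for finding side effects, and the article does not say how one feeds the other. A symptom disclosed only because staff asked was not volunteered, and a symptom such as dizziness is hardly observable. One site could enter it as an AE and another could leave it out, both following the text.

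The volunteered route also depends on what the participant knows. Everyone knows who takes SFOH, so willingness to mention a symptom, or to attribute it to treatment, may differ between arms C and D on one side and A and B on the other.

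Finally, the structured questionnaire has two fixed time points, and nothing shown provides for it when someone stops medication or leaves.

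The trial aims to give a rationale for early treatment of patients without hyperphosphatemia, for whom tolerability weighs heavily. No data safety monitoring board is set up, so the by-arm AE table is the main comparative harm output described.

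**Working it through.** **1. Which listed AEs are exposed.** The list in {22} has eight clinical items and two laboratory items. Five of the eight depend largely on what the participant says: gastro-intestinal complaints, muscle weakness, somnolence, dizziness and taste disturbance. Arrhythmia, fracture and tooth discoloration are more open to observation. The plasma magnesium and phosphate limits are laboratory values, which knowledge of SFOH does not affect.

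**2. Which contrasts are exposed.** SFOH status is the same within A versus B and within C versus D, and magnesium is blinded, so knowledge of SFOH does not distort those two contrasts. C or D against A or B crosses the open-label boundary.

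**3. What differential reporting could do (assumed rates, none from the article).** If the true risk p is equal in both pairs of arms, and the recorded fractions are r1 and r2, the false risk difference is p × (r2 − r1).

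| p | r2 − r1 = 0 | 0.2 | 0.4 |
|---|---|---|---|
| 10% | 0 | 2 points | 4 points |
| 20% | 0 | 4 points | 8 points |
| 30% | 0 | 6 points | 12 points |

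The sign follows whichever pair of arms reports more completely, and the article does not fix that.

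**4. The plan's own drop-out figure.** Inputs from Sample size {14}: difference 1.0 m/s, SD 2.0 m/s, rho 0.7, power 80%, two-sided 0.05, drop-out 15%.

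- SD of change = 2.0 × √(2 × (1 − 0.7)) = 1.549 m/s.
- n = 2 × (1.960 + 0.842)² × 1.549² / 1.0² = 37.7, so 38 per group.
- 38 / 0.85 = 44.7, so 45 per group and 180 in total. This reproduces the plan.
- Expected leavers per arm: 0.15 × 45 = 6.75, about 7.

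**5. What leavers could do to the AE table (assumed counts).** Suppose 14 of 45 (31.1%) in an arm have a listed symptom and all 7 leavers are among them.

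- None of the 7 captured by any route: (14 − 7) / 45 = 15.6%.
- Half captured: (14 − 3.5) / 45 = 23.3%.
- All captured: 14 / 45 = 31.1%, no loss.

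The result depends wholly on the capture fraction, which the article does not give. If no leaver is symptomatic, there is no loss either.

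**The case against.** The strongest reply is that the two sections can be read together. A complaint that staff identify during the active check could count as observed by research staff, and nothing says that such complaints are discarded. That reading is possible, but it is not stated, and for a symptom it stretches the word. The inconsistency therefore stands as a risk, not as a proven loss.

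A reader might infer three stronger points that the article does not support:

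- *That side effects are asked about only at weeks 6 and 24.* This is contradicted by {11c}. Only the structured form is limited to those weeks.
- *That patients who cannot tolerate treatment are missed.* The PWV request in {18b} concerns people who discontinue participation, and it does not say that nothing else will be collected. Those who stop or modify treatment have follow-up under {11b} and Fig. 1, and the intention-to-treat rule keeps them in the efficacy analysis. Someone who stops because of a complaint will often have voiced it, and it is then recordable under {22}.
- *That drop-out roughly halves the recorded AE rate.* That needs every leaver to be symptomatic and none to be captured. A similar fall could appear among week-24 questionnaire completers under assumed counts, but that is not the AE table, which is nowhere restricted to completers.

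It is also fair that an article condenses a fuller protocol, that harms are descriptive here, and that asking identical questions does not blind anyone to SFOH. Identical questions do, however, remove the part of the difference that comes from who chooses to speak up.

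**Conclusion.** The point holds as an inexpensive improvement. As written, {11c} and {22} do not say whether a symptom disclosed on questioning is recorded as an AE. The Discussion's defence of the open label does not extend to AEs, so volunteered symptoms may be reported differently across the SFOH boundary. Early leavers may be under-represented in the side-effect data, because the form is given at two fixed weeks and {18b} names no harm assessment for them.

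Neither the direction nor the size of any bias can be established from the article. The 2 to 12 point range assumes true risks of 10% to 30% and a reporting gap of 20 to 40 points; with no gap it is zero. Laboratory AEs, and reporting within A versus B and C versus D, are not affected by knowledge of SFOH. Fig. 1 or the full protocol may already cover part of the gap for those who stop treatment.

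**What to change.** 1. In {22}, replace reliance on volunteered or observed symptoms with elicitation of one fixed symptom list, in the same words and in all four arms, at each scheduled visit. Record the answers as AEs, so that the active check in {11c} feeds the AE table. Keep recording events that are volunteered or observed between visits.
2. Flag each AE in the eCRF as elicited or spontaneous, and show the two separately in the by-arm table.
3. Offer the existing questionnaire when study medication is stopped or participation ends, and in {18b} request it together with the T3 PWV. An additional week-12 questionnaire is optional.
4. Tabulate AEs by arm over all randomised and treated participants.

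**Cost:** changes to eCRF and visit-form wording, and a few minutes per visit with a form that already exists. AE counts will rise in all arms. Recruitment began in July 2020 and is described as ongoing, so the table would mix two methods of ascertainment. The change applies equally to all arms, and AEs should be reported by period, before and after it.

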#### Frequency and plans for auditing trial conduct {23}

All study sites will be monitored by an independent monitor of the CRB of the Amsterdam UMC, location VUmc. In addition to a preparatory and closing visit, each study site will have monitoring visits every 6 to 12 months. The monitors will review the source documents to determine whether the data reported in the eCRF are complete and accurate. Also correct use of inclusion and exclusion criteria, data protection as well as medical research products will be verified.

#### Plans for communicating important protocol amendments to relevant parties (e.g., trial participants, ethical committees) {25}

In case of any substantial change in the protocol, an amendment will be submitted to the METC and the CA and the research team and participants will be notified. If applicable, also the participant information letter, the informed consent form, study operator manuals, and trial registrations will be updated. After the start of the study, one substantial amendment has been submitted. The current study protocol (version 3.3, 15 April 2021) is approved on 28 April 2021. Changes in the original approved protocol are summarized in Additional file 3.

#### Dissemination plans {31a}

All results will be reported in medical journals with immediate open access conform the NIGRAM2+ consortium agreement, regardless of results. When granted the opportunity, the results will be presented at national and international conferences. Main study results will be communicated actively to all health care professionals and participants that participated in the study. Also the Dutch organization for Kidney patients “Nierpatiënten Vereniging Nederland” will be approached for dissemination to their members, and we aim to highlight our results through https://www.niernieuws.nl/ and similar kidney patient platforms.

## Discussion

This study is the first multi-center, randomized controlled trial assessing the combined effect of magnesium citrate and the phosphate binder SFOH on arterial stiffness, calcification, and inflammation parameters in people with stage 3 and 4 CKD, based on the understanding that increasing magnesium and improving phosphate homeostasis could synergistically retard the progression of established vascular calcification [19], and people with moderate CKD could benefit most. To our knowledge, only two oral magnesium intervention studies in patients with moderate CKD have been performed so far [53, 54]. A 2-year open-label randomized trial in stage 3–4 CKD patients demonstrated a statistically significant smaller median increase in coronary artery calcification (11.3% versus 39.5%) for participants treated with magnesium oxide as compared to the control group [53]. Another RCT in a comparable population with moderate CKD resulted in a significant increase (improvement) of T_50_ of 40 min (95% confidence interval 11–70 min, *P* <0.05) compared to placebo, after 8 weeks of oral magnesium hydroxide supplementation [54]. Different form the established effects of phosphate binders on correcting hyperphosphatemia, these effects of phosphate-lowering therapy in moderate CKD in the absence of hyperphosphatemia are not yet well established [43–45, 55, 56]. In this study, the non-calcium based phosphate binder SFOH is prescribed because of its relatively low pill burden compared to other phosphate binders [47] and to avert the potential confounding effect on vascular calcification due to calcium content. The explorative ^18^F-FDG and ^18^F-NaF PET-scans will also contribute to the understanding of important pathophysiological mechanisms of arterial wall inflammation and calcification, respectively. A recent study in CKD patients without overt atherosclerotic disease observed increased arterial wall inflammation through ^18^F-FDG PET imaging, compared to healthy controls. ^18^F-NaF PET-scans conceivably enable microcalcification formation detection, even before macroscopic calcification is revealed through regular CT techniques. Moreover, the lack of ^18^F-NaF uptake in macroscopic calcified vessel walls supports the theory that ^18^F-NaF only binds to active calcification deposition and therefore studies an early or active phase of arterial calcification. It is in this early phase, that modulating magnesium and phosphate might prove most beneficial.

Several clinical and preclinical studies support the potential of combined magnesium and phosphate interventions. In vitro, the presence of high magnesium levels can prevent the phosphate-induced phenotypic switch of vascular smooth muscle cells of the intima media into bone forming cells and additionally is an inhibitor of the formation of precipitating calcium-phosphate products (hydroxyapatite nanocrystals) [21, 57, 58]. In clinical setting, high magnesium concentrations are associated with lower calcification propensity (i.e., higher T_50_ values), inhibition of the phosphate containing CPP formation rate, and with lower FGF23 levels [54, 59].

Strengths of this study include the possibility to investigate magnesium citrate and sucroferric oxyhydroxide as modulators of vascular calcification synergically and separately on various parameters of interest. By additionally measuring the T_50_, we will be able to investigate if the presumed effect on arterial stiffness is mediated by calcification propensity. The study design with repeated measurements of primary and secondary outcomes allows for thorough statistical analyses and a reduced number of participants. This design also allows for studying the intervention effects over time, i.e., at 12 weeks, 24 weeks, and after a wash-out period. The main limitation of this study is the fact that arterial stiffness is only a intermediate marker of CVD and has some degree of operator dependency. However, the association of PWV and cardiovascular disease and mortality is well established in the CKD population [11–14], and intervention effects can be detected already after 6 months [17, 18]. The PWV measurements will be performed by a limited number of well-trained study personnel, aiming at measurements performed on an individual participant by the same operator, thereby limiting the effect of inter-operator variability.

A limitation of the study design is the open-label phosphate binder intervention with SFOH chewing tablets. A double-blind design with a SFOH placebo was not feasible, due to the notable structure, color, and taste of these tablets and the frequently encountered side effect of stools discoloration. However, the primary and secondary outcomes are standardized measurements and therefore unlikely to be influenced by this knowledge. Another limitation of this study is the fact that CKD patients frequently receive dietary consultation, stimulating a more healthy diet and specifically targeting potassium and phosphate intake. Therefore, subsequent dietary changes during the follow-up period could influence magnesium and phosphate levels. However, good quality dietary records are notoriously difficult and therefore we did not consider this in our analysis.

This RCT will add knowledge on calcium-free phosphate binder therapy in normophosphatic patients with stage 3–4 CKD, and it investigates the effects of a magnesium supplement as potential intervention to improve vascular function. By doing so, this study aims to provide a rationale to early treatment for people with moderate CKD to reduce the high burden of CVD in this population.

## Trial status

Current trial status is ongoing. The study started 15 July 2020 with temporarily halt of recruitment due to COVID-19-related restrictions. Recruitment is expected to be completed in 2023 if COVID-19-related restrictions do not further hamper study recruitment.

## Data Availability

The NIGRAM2+ consortium agreement is leading regarding data availability and publication.

## Abbreviations

AE: Adverse event
AMC: Academic Medical Center (together with VUmc ‘Amsterdam UMC’)
AVG: Personal Data Protection Act. Dutch translation: Algemene verordening gegevensbescherming, formerly mentioned as Wet bescherming persoonsgegevens (Wpb)
BMI: Body mass index
CA: Competent authority
CCMO: Central Committee on Research Involving Human Subjects; in Dutch: Centrale Commissie Mensgebonden Onderzoek
CKD: Chronic kidney disease
CPP: Calciprotein PARTICLES
CT: Computer TOMOGRAPHY
CVD: Cardiovascular disease
DSMB: Data Safety Monitoring Board
eCRF: Electronic case report form
ECG: Electrocardiography
eGFR: Estimated glomerular filtration rate
EPD: Electronic patient dossier
ESRD: End-stage renal disease
EudraCT: European Drug Regulatory Affairs Clinical Trials
^18^F-FDG: Fluor-18-deoxyglucose
^18^F-NaF: Fluor-18-sodium fluoride
FGF23: Fibroblast growth factor 23
KDIGO: Kidney Disease Improving Global Outcomes; global nonprofit organization developing and implementing evidence-based clinical practice guidelines in kidney disease
hsCRP: High-sensitivity C-reactive protein
ISF: Investigator site file
METC: Medical research ethics committee (MREC); in Dutch: medisch ethische toetsing commissie
mmol/L: Millimole/liter (0.001 mol per liter)
MDS: Most diseased segment
NIGRAM2+: Nijmegen Groningen Amsterdam consortium and acronym for ‘Nier Gericht Research van Arterie tot Mens’ with the 2+ referring to the follow-up of the first NIGRAM consortium, and the focus on the Mg^2+^ ion
OLVG: Onze Lieve Vrouwe Gasthuis
PET: Positron emission tomography
PMM: Predictive mean matching
RAS: Renin angiotensin system
ROI: Region of interest
iPTH: Intact parathyroid hormone
PWV: Pulse wave velocity
SAE: Serious adverse event
SD: Standard deviation
SFOH: Sucroferric oxyhydroxide
Sponsor: The sponsor is the party that commissions the organization or performance of the research, for example a pharmaceutical company, academic hospital, scientific organization or investigator. A party that provides funding for a study but does not commission it is not regarded as the sponsor, but referred to as a subsidizing party
SUSAR: Suspected unexpected serious adverse reaction
SUV: Standardized uptake value
T_50_: Calcification propensity (also referred to as CPP maturation time or calcification blood test)
TBR: Target to background ratio
TMF: Trial master file
UMC: University Medical Center(s)
UMCG: University Medical Center Groningen
VSMC: Vascular smooth muscle cell
VUmc: VU medical center (in Dutch: Vrije Universiteit medisch centrum)
WMO: Medical Research Involving Human Subjects Act (in Dutch: Wet Medisch-wetenschappelijk Onderzoek met Mensen
X-LWK: X-Lumbale Wervel Kolom, an X-ray of the lower back displaying the abdominal aorta
